## Abstract

**Background:**

Coronary heart disease (CHD), is the major contributor to cardiac-associated mortality worldwide. Lifestyle modification, including physical activity, is highly recommended for secondary prevention for patients with CHD. However, many people in Sri Lanka with CHD do not engage in adequate physical activity.

**Objective:**

To develop a culture-specific, motivated, and action-based intervention and examine its effects on physical activity level, exercise self-efficacy, and cardiovascular risk factors among patients with CHD.

**Methods and materials:**

This is an assessor-blinded randomized controlled trial that will recruit 150 patients with CHD from the inpatients cardiac unit of a hospital in Batticaloa, Sri Lanka, and will randomly assign them either to the intervention group or the control group. The participants in the intervention group will receive a culture-specific and motivated, action-based intervention in addition to the usual care, while participants in the control will only receive the usual care. The intervention consists of a face-to-face preparatory session and 12-week motivated, action-based sessions which were developed based on the health action process approach (HAPA) framework. The face-to-face preparatory session will identify the health needs of the participants, develop a goal-oriented patient-centered action plan, and provide knowledge and an overview of the program. The 12-week motivated, action-based sessions consist of three monthly group education and center-based group exercises, followed by three 20-min individualized telephone follow-ups. Outcomes will be assessed immediately after the intervention and at one-month post-intervention.

**Discussion:**

This protocol proposes a supervised centered-based group exercise with group education, and individualized telephone follow-ups guided by the HAPA framework to improve the physical activity level, exercise self-efficacy, and cardiovascular risk factors of patients with CHD. Results from this study will inform the effectiveness of a motivated, action-based intervention in a low-resource setting and provide information on the feasibility, barriers, and facilitators for lifestyle modification in Sri Lanka.

**Trial registration:**

ClinicalTrial.gov.org PRS: NCT05051774; Date of registration: September 21, 2021.

## Introduction

Coronary heart disease (CHD), a major group of cardiovascular disorders (CVDs), is one of the major contributors to cardiac-associated mortality worldwide, including in Sri Lanka which, causes 8.9 million deaths worldwide in 2019 [1, 2], and an evolving health issue in developing countries; its mortality is declining around the globe [3]. In low-middle income countries like Sri Lanka, death and premature death associated with CHD in all age groups increased by 15.6% and 5% from 2009 to 2019 [4]. Modifiable risk factors, such as physical inactivity, smoking, consumption of an unhealthy diet and alcohol, elevated body mass index (BMI), high blood pressure, elevated serum lipids, and elevated fasting blood glucose levels are common among patients with CHD [5, 6]. Prolonged exposure to these preventable risk factors increases the risk of recurrent cardiac events and premature death and leads to poor prognosis among patients with CHD [7]. CHD is one of the major contributors to disability-adjusted life years (DALYs), and the total number of CHD-associated DALYs has gradually increased since 1990, reaching 182 million in 2019 [8].

Cardiac rehabilitation (CR), a well-established recommendation for secondary prevention in patients with CHD, comprises six core components, namely, health behavior change and education, lifestyle risk factor management, psychosocial health, medical risk management, long-term strategies, and audit and evaluation. CR is effective in reducing all-cause mortality, cardiac mortality, myocardial re-infarction, and cardiovascular risk factors and improving physical activity and quality of life in high, low, and middle-income countries [9, 10]. Although comprehensive CR is effective in improving the health outcomes of patients with CHD, its availability worldwide is only 38% because of inadequate physical and financial resources [11]. Providing a center-based CR is particularly difficult in South Asia including Sri Lanka because of the lack of human resources, space and equipment, and financial support [11, 12]. Therefore, effective strategies for the secondary prevention of CHD are urgently needed.

Lifestyle modification, including physical activity, is one of the key recommendations for secondary prevention for patients with CVDs [13]. A systematic review and meta-analysis of 85 randomized controlled trials (RCTs) that included people with CHD reported that engaging in physical activity contributes to a substantial reduction in all-cause mortality, cardiovascular mortality, recurrent cardiac events, and improvements in health-related quality of life (HRQoL) [14]. However, inadequate physical activity is common among people with CHD in both developed and developing countries, and its prevalence ranges from 56.7% (Sri Lanka) to 83% (United States) [15, 16].

With the increasing morbidity and mortality rate from CHD, especially in low- and middle-income countries, secondary prevention including exercise-based CR plays an important role in improving the prognosis of patients with CHD [7, 17]. High prevalence of physical inactivity, unhealthy dietary practices, poor control of blood glucose, blood pressure (BP), blood lipid, and body weight (BW) was found among patients with CHD in the world, as well as in Sri Lanka [16, 18–20]. Therefore, a culturally appropriate intervention must be designed and implemented using a theoretical framework to improve the physical activity level, exercise self-efficacy, and cardiovascular risk factors in patients with CHD in Sri Lanka.

### Health action process approach (HAPA)

The intervention is underpinned by the HAPA framework to enhance an individual transitioning the intention into action. HAPA is a social-cognitive framework specifying motivational and volitional determinants of health behavior [21], and it is used to guide various health promotion interventions, such as promoting adequate physical activity [22] and dietary behaviors [23]. HAPA comprises two phases, namely, the motivation phase and the volition phase, which emphasizes the initiation and maintenance of health behaviors.

HAPA uses a patient-centered collaborative approach that assesses patients’ beliefs on their health problems experienced, their confidence to perform the assigned action, and their expectations to initiate the intention and form target goals and action plans for behavioral change. Inter-active teaching and exercise can help the participants enhance their knowledge and skills to improve their confidence to transform the intention into action. Individual confidence is also important in dealing with barriers that arise during behavioral action, such as resuming difficult behavior after an interruption and helping continue the achieved desired behavior [21].

## Methods and materials

### Aims and study design

This assessor-blinded, two-arm parallel RCT aims to develop a culture-specific, motivated, and action-based intervention and examine its effects on physical activity level, exercise self-efficacy, and cardiovascular risk factors of patients with first-onset CHD in Sri Lanka.

### Study setting

The study will be conducted at the cardiology clinic of the university-affiliated Teaching Hospital Batticaloa, Sri Lanka, where patients with CHD are treated and discharged under stable medications or referred to another hospital for further conservative management such as percutaneous coronary intervention or coronary artery bypass graft. There are around 360 newly diagnosed patients with CHD are admitted to this hospital each year.

Study participants will be patients newly diagnosed with CHD that are admitted to the cardiac unit and medical wards of the Teaching Hospital Batticaloa, Sri Lanka. The intervention will be delivered at the study hospital’s cardiology clinic. All CHD patients of the study clinic will receive multidisciplinary services including monthly medical check-ups, unstructured health education on a healthy lifestyle, and a brief session on managing diseases, risk factors, and stress provided by a team including cardiologists, physicians, nurses, and other health care workers. Cardiac patients attending other OPD services are also referred to the cardiac clinic for health assessment and unstructured health education.

### Study participants/eligibility criteria

Eligibilities of the participants are adults aged 18 years and above, hospitalized with CHD for the first time, diagnosis confirmed by electrocardiogram or angiography within 6 months, able to read and speak Tamil, obtained a medical clearance from a cardiologist to perform the exercise, and no prescribed activities or exercise restriction. The exclusion criteria are as follows: absolute and relative contradictions to exercise testing and training or at high risk for exercise prescription according to the American College of Sports Medicine guideline and American Association of Cardiovascular and Pulmonary Rehabilitation guideline [24]; any diagnosis of life-limiting conditions; a diagnosis of acute psychotic disease; and unable to independently perform physical activities. Eligible participants will be identified by the research nurse from the coronary care unit and medical wards of the study hospital by reviewing their medical records. In addition, the cardiologist and physiotherapist at the study hospital will be consulted to confirm the suitability of the participants that will perform the interventional exercise.

### Sample size estimation

The sample size estimation is based on the primary outcomes of the study, namely, the physical activity level. Referring to the findings of the literature review, the effect size on improving physical activity is from 0.5 [25] to 0.8 [26]. Therefore, the smallest effect size of 0.5 [25] will be considered in calculating the sample size for this study. To achieve a power of 1-β = 0.8 with a significance level of 0.05 (two sides) and account for 14% of the attrition rate [27] of the previous study, a total of 150 participants will be recruited in this study.

### Randomization, blinding, and data collection procedure

All eligible participants will be invited to participate in this study, and a thorough explanation of the study by using the information sheet will be provided by the researcher (Fig 1). Informed consent will be obtained from the participants by the researcher before the study begins. All eligible participants will be classified as either male or female because gender influences the level of physical activities among patients with CHD [28]. The participants will be randomized either to an intervention or control group with a ratio of 1:1 using block randomization with a block size of eight. Random sequencing for group allocation will be generated by an online application (http://www.randmization.com). The group allocation will be placed into an opaque sealed envelope and will be given to the participants after baseline data collection (T_0_) by the research assistant who is independent of the study. The participants will not be blinded to their group allocation because of the nature of the study. The outcomes will be evaluated after completiing the 12-week intervention (T_1_) and one-month post-intervention (T_2_) by a trained research assistant blinded to the participants’ allocation (Fig 2). The outcomes that will be evaluated are the physical activity level, exercise self-efficacy, and cardiovascular risk factors. Every participant will receive 230 Sri Lankan rupees (1 United States Dollar) after completing the data collection to compensate for their time spent on data collection.

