### Motivated action-based intervention

To initiate and maintain the positive behavioral changes and health outcomes of patients with CHD, who are discharged from the study hospital, the motivated action-based intervention is developed according to the HAPA framework. The intervention will be provided in two phases: 1) a brief face-to-face preparatory phase, and 2) a 12-week intervention phase using the HAPA framework. The researcher, a registered nurse with extensive experience in clinical teaching and patient education, will be involved in delivering the intervention with support from the cardiologist, medical doctor, cardiac nurses, and physiotherapist to optimize the patients’ outcomes.

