#### Face-to-face preparatory phase

The preparatory phase includes one individualized health counseling session for 60 min and it will be conducted by the researcher at the study hospital’s cardiology clinic within 6 months after the CHD event. During this session, the participant’s health needs will be recognized by assessing the health condition, reviewing the daily activities, exploring the discrepancy between activity levels, and the recommended exercise guidelines, identifying the three desired outcomes (achievable and observable) and forming individualized exercise goals and a behavior-specific action plan for behavioral changes. In addition, knowledge and an overview of the program and real success stories will be shared with the participants.

The self-reported risk of CHD will be compared with the calculated Framingham risk score in identifying the discrepancy in the risk level and enhancing the risk perception of participants. In addition, the participants’ concerns and questions will be addressed in this phase to alleviate their fear and anxiety to perform the exercise and enhance their knowledge of CHD.

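### One fixed, disclosed block size of eight at a single open-label site, where the same researcher takes consent and delivers the intervention, makes upcoming allocations partly predictable

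*Protocol article*

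**What the plan says.** All references are to the Protocol article.

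- **Allocation.** Randomization, blinding, and data collection procedure specifies allocation "with a ratio of 1:1 using block randomization with a block size of eight". It mentions no variation in block size and no step to keep the size from recruiting staff.
- **Sex.** The preceding sentence reads: "All eligible participants will be classified as either male or female because gender influences the level of physical activities". The text does not say that randomization is stratified. Separate blocks for men and women are the natural reading, but an inferred one.
- **Consent.** The same section states: "Informed consent will be obtained from the participants by the researcher before the study begins". The researcher also explains the study to each candidate.
- **Delivery.** Motivated action-based intervention states: "The researcher, a registered nurse with extensive experience in clinical teaching and patient education, will be involved in delivering the intervention". Face-to-face preparatory phase describes "one individualized health counseling session for 60 min and it will be conducted by the researcher". Under Intervention phase the researcher gives the group education, implements the exercise sessions with support, and shares the telephone calls with a trained research assistant.
- **Setting and blinding.** There is one site (Study setting: "The study will be conducted at the cardiology clinic of the university-affiliated Teaching Hospital Batticaloa, Sri Lanka"), and allocation is open to participants: "The participants will not be blinded to their group allocation because of the nature of the study".
- **Safeguards.** Allocations are in opaque sealed envelopes, handed over after baseline measurement by a research assistant independent of the study. All eligible patients are to be invited. The cardiologist and physiotherapist are consulted on suitability for the exercise (Study participants/eligibility criteria).

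**The concern.** The person who consents everyone also sees who comes to the individual preparatory session. Those participants are in the intervention arm; a consented participant who gets no session is, in time, recognizable as a control. With a single known block size, four of one arm among the allocations so far in a block fix the rest of that block. A sealed envelope hides the next allocation but does not hide the past ones from which it can be deduced.

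The exposed decision comes before the envelope: whom to approach, when, and how persuasively. If more motivated patients were steered towards expected intervention slots, the arms would differ in motivation at entry. The primary outcome is self-reported physical activity (IPAQ-SF) in a trial of a motivational intervention, so such selection would act directly on the result.

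**Working it through.** **The plan's own figure.** The article gives no figure for predictability. The only number to reproduce is the sample size (Sample size estimation: effect size 0.5, power 0.8, two-sided 0.05, attrition 14%). A two-sample t-test needs 63.8, so 64 per arm. Then 64 / (1 − 0.14) = 74.4, so 75 per arm and 150 in total. The stated 150 reproduces and is not affected by this point.

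**Inputs for predictability.** Block size 8, ratio 1:1, so b = 4 per arm and C(8,4) = 70 equally likely blocks.

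**Certain assignments, all earlier allocations known.** An assignment is certain once the earlier part of the block contains all four of one arm. The number of blocks, out of 70, in which this holds is:

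| Earlier allocations known in the block | 4 | 5 | 6 | 7 |
|---|---|---|---|---|
| Blocks in which the next is certain | 2 | 10 | 30 | 70 |

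The sum is 112/70 = 1.6 per block of 8, or 20%, which agrees with 1/(b + 1) = 1/5. Over a trial of 150 with incomplete last blocks, simulation gives 19.1% with strata of 75 and 75, 19.2% with 105 and 45, and 19.5% with a single list. That is about 29 of 150 (0.191 × 150 = 28.7; 0.195 × 150 = 29.3). The strata sizes are assumptions, and the result hardly depends on them or on whether sex is a stratum at all.

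**Best-guess rate, all earlier allocations known.** [b + (4^b / C(2b,b) − 1)/2] / (2b) = [4 + (256/70 − 1)/2] / 8 = 5.329 / 8 = 66.6% for complete blocks. The simulated trial of 150 gives about 66%.

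**Delay in learning allocations.** If the latest L allocations in the stratum are unknown, the counts above shift L places later in the block:

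| Latest allocations unknown | Certain share | Best guess right |
|---|---|---|
| 0 | 112/(70 × 8) = 20% | 66.6% |
| 1 | (2 + 10 + 30)/560 = 7.5% | 60% |
| 2 | (2 + 10)/560 = 2.1% | 58% |
| 3 | 2/560 = 0.4% | 55% |

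The guess rates come from enumerating all 70 blocks.

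**Varying block sizes.** These were simulated over 150 patients, 400 runs, with a guesser who knows the set of sizes and every past allocation:

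| Sizes | Certain share | Best guess right |
|---|---|---|
| 8 only | 19–20% | 66% |
| 4, 6, 8 | 2–3% | 68% |
| 6, 8, 10 | 2% | 66% |
| 4, 8 | 7% | 68% |

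**The case against.** The strongest reply is that the 20% and 66% figures describe a recruiter who knows every earlier allocation, in order, before each new consent. The article does not describe that. The independent assistant hands over the envelope. The preparatory session is timed only relative to the coronary event (within six months), and control status gives no positive signal. Study setting reports around 360 new patients a year, or 360/52 ≈ 7 a week before eligibility and refusal, so even a short delay could leave the latest few allocations unknown. This stands: the figures are a ceiling, and the range by delay must go with them. But the article sets no interval between allocation and session, so delay is not a planned protection.

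The safeguards also count. Inviting all eligible patients, the clinical suitability check, baseline before allocation and independent hand-over all leave less room to act on a guess. None of them prevents deduction from past allocations, and none governs the order of approach or the persuasion used.

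A reader might infer that any resulting bias would be beyond repair in the analysis. That goes too far. Physical activity and exercise self-efficacy are measured before allocation, and Data analysis plans a generalized estimating equation with confounder adjustment. Adjustment could remove the measured part of an imbalance. Motivation itself is not among the baseline variables listed, so that part would remain.

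A reader might also infer that the allocation list is in the wrong hands. The article does not say who generates or holds it, and a condensed article may leave that to the full protocol. It is not part of this point.

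**Conclusion.** The point holds in a limited form. A fixed, disclosed block of eight, used where one person both consents and delivers in an open-label single-site trial, leaves allocations partly predictable. The upper bound is about 19–20% certain (about 29 of 150) and about 66% guessable. With the latest one to three allocations unknown, the range is 7.5% down to 0.4% certain and 60% down to 55% guessable.

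This rests on three assumptions: the researcher knows the block size, which the protocol prints; the term researcher means the same person in the consent and delivery sections; and blocks run within sex, although a single list gives almost the same result.

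A reader might go further and conclude that allocation is simply predictable, or that concealment has failed. The documents do not support that: most assignments remain uncertain even at the ceiling, the delay is unknown, and nothing shows that anyone would act on a guess. The risk is one of selection bias, not of sample size or power.

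**What to change.** Replace the fixed block of eight with randomly varying block sizes within sex, for example 6, 8 and 10, or 4, 6 and 8. State explicitly that randomization is stratified by sex, if that is meant. Withhold the sizes from the person who recruits and consents. If recruitment has started, apply this to the remaining envelopes.

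This reduces certain assignments from about 19–20% to about 2%. It does not reduce average guessing by someone who knows the set of sizes and all past allocations: that rate stays at about 66% with 6, 8 and 10 and about 68% with 4, 6 and 8. Only keeping the sizes or the past allocations from the person taking consent acts on that part, and the size of that gain was not calculated.

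The cost is a regenerated list and new envelopes, with slightly looser balance between arms if larger blocks are used. The sample size stays at 150.

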**Fig 1 pone.0270800.g001:**
[figure not shown]
SPIRIT schedule of enrolment, intervention, and assessment of the outcomes.

**Fig 2 pone.0270800.g002:**
[figure not shown]
Flow diagram of the study protocol.

### Motivated action-based intervention

To initiate and maintain the positive behavioral changes and health outcomes of patients with CHD, who are discharged from the study hospital, the motivated action-based intervention is developed according to the HAPA framework. The intervention will be provided in two phases: 1) a brief face-to-face preparatory phase, and 2) a 12-week intervention phase using the HAPA framework. The researcher, a registered nurse with extensive experience in clinical teaching and patient education, will be involved in delivering the intervention with support from the cardiologist, medical doctor, cardiac nurses, and physiotherapist to optimize the patients’ outcomes.

#### Face-to-face preparatory phase

The preparatory phase includes one individualized health counseling session for 60 min and it will be conducted by the researcher at the study hospital’s cardiology clinic within 6 months after the CHD event. During this session, the participant’s health needs will be recognized by assessing the health condition, reviewing the daily activities, exploring the discrepancy between activity levels, and the recommended exercise guidelines, identifying the three desired outcomes (achievable and observable) and forming individualized exercise goals and a behavior-specific action plan for behavioral changes. In addition, knowledge and an overview of the program and real success stories will be shared with the participants.

The self-reported risk of CHD will be compared with the calculated Framingham risk score in identifying the discrepancy in the risk level and enhancing the risk perception of participants. In addition, the participants’ concerns and questions will be addressed in this phase to alleviate their fear and anxiety to perform the exercise and enhance their knowledge of CHD.

